### Eligibility criteria for staff delivering the interventions

Staff delivering the new intervention have been selected on the basis of their experience of working in a high-support way on similar interventions such as the *Emerge Mount Street Employment*^2^ initiative and the *Ballymun Youth Guarantee*^3^ pilot. Staff must also have relevant training and skills in the use of key guidance approaches and tools (e.g. interest inventories, vocational counselling skills, motivational interviewing).

## Interventions

### The EEPIC intervention

The new EEPIC intervention is a high-support therapeutic guidance programme which focuses on the development of a career plan and strengthening the human, social and psychological capital required to implement this plan**.** The intervention consists of a four-stage process (see Fig. 2), which typically lasts 8–12 weeks, and which aims to support the job-seeker in developing the skills necessary for labour market access while building self-efficacy and esteem and improving psychological wellbeing:*Stage 1:* The individual’s needs (education, training, skills, personal situation, employment history, perceived employability competencies, work values, barriers to employment, wellbeing, etc.) are assessed using a Profile Form adapted from the Ballymun Youth Guarantee (Ballymun Job Centre, 2013) and EMERGE (Ballymun Job Centre, 2010–2012) initiatives. Identification of specific needs and their severity is vital in understanding the barriers faced by the individual and the types of supports and actions required to enable them to move towards the labour market. The outcome of the individual needs assessment determines the extent to which guidance practitioners may need to support the individual to engage with appropriate services to address issues which pose barriers to progression (e.g. addiction, literacy). Interaction with other services and supports are documented by the practitioner in their case notes.*Stage 2:* A tailored career guidance process is implemented to support the job-seeker in identifying latent skills, abilities, aptitudes, preferred behaviour style in the workplace and values. This process aims to build career clarity, career identity and improve self-esteem and career efficacy. Vocationally orientated career guidance tools and approaches (e.g. career interest inventories, general and specific aptitude assessments, person-centred vocational counselling) are used to reveal hidden strengths, aptitudes and preferences, while limitations are also acknowledged and documented. This information is used to inform the development of a detailed career plan.*Stage 3:* The job-seeker and guidance practitioner work together to develop a career plan which includes a career objective or aspiration, a number of shorter-term career goals which should be SMART (Specific, Measurable, Achievable, Realistic and Time-bound) and potential barriers to progression. A timescale for this plan is also identified and a method to achieve it is discussed, particularly in relation to responsibilities and extent of contact required (e.g. weekly/fortnightly meetings with the guidance practitioner).*Stage 4:* The career plan is implemented in a supportive and positive way. This involves the job-seeker and the practitioner working together to accomplish the planned career goals, to maintain levels of motivation, to build resilience against setbacks and adapt and re-plan as required.

**Fig. 2 Fig2:**
[figure not shown]
Four Stage EEPIC Intervention Process

This intervention is implemented on a one-to-one basis with the guidance practitioner and the client working together to identify key strengths, career identity and learning needs. The successful implementation of a career plan relies heavily on the client–practitioner relationship and commitment to the plan. This intervention is, therefore, highly dependent on the skills and approach of the practitioner involved in delivering the service. It also relies on the continuum of support offered so that the client is supported throughout their journey toward, and into, the labour market. This involves building networks with those who can offer support, such as mentors within the education and training sector and within the workplace.

### Adherence to intervention protocol

Face-to-face adherence meetings will be held with practitioners to monitor participant progress and their adherence to the intervention. These meetings will form part of the already established guidance sessions which are held bi-monthly and are attended by the guidance team leader and the guidance practitioner with the purpose of reviewing progress. The lead investigator (psychologist) will attend these meetings and monitor adherence to the intervention and study protocol.

Participants will be permitted to attend additional support services with which they are in contact before trial entry or identified as appropriate to their needs during the trial. These support services include primary healthcare, addiction supports and community services, but exclude other employment support services. Participants who are referred by the DSP to an alternative employment support service either before their entry to the study or who are referred during the trial will be ineligible for participation.

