### Sample size

A power analysis was conducted using the primary outcome measure of overall psychological wellbeing (GHQ-12) in order to identify the minimum sample size required to detect an increase in wellbeing post intervention. As already indicated, the Pathways to Work activation model is a recently implemented approach and so no previous evaluations or comparable studies have been undertaken, although similar studies had been conducted in Sweden [51], France [52], Australia [6] the UK [41, 42] Finland [72] and the USA [53, 73]. Analysis of these studies indicate varying sample sizes (*n* = 16–1200); thus, to ensure the minimum sample size is achieved and the study is powerful enough to detect significant differences between the groups, a power analysis was performed to establish a realistic estimate based on the primary outcome measure. This analysis was conducted for an independent samples t-test, as this is expected to be the least powerful test in the overall main analysis. The analysis was two-tailed (alpha of 0.05), as we do not know in advance which group will perform better in GHQ-12 terms. G*Power t-test calculations for the difference between two independent means (two groups) show that for the current study, 128 unemployed participants (64 in each group) will be sufficient to detect a change of 0.50 (medium) at 80% power and at 5% significance at a given time point. An allowance of (approximately) 10% will be made for possible attrition, so the actual sample size target will be 70 per group. This should be more than sufficient for Mixed Model Repeated Measures (MMRM) across the three time points to have > 80% power and also allow for post-hoc t-tests both between groups and within groups to have ≥ 80% power.

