### Blinding

After assignment to the respective interventions, the participants are blinded to allocation for the duration of the study. The researcher who performs the assessments at baseline is also blinded until the completion of baseline assessments. Due to the nature of the intervention, the staff delivering the interventions cannot be blinded and are instructed not to disclose information to either the researchers or the participants which may indicate which intervention the participant is receiving. Blinding of the researcher cannot be maintained post baseline as the researcher is also responsible for data collection in this study. For the participant, it remains unclear which intervention is being received as both interventions occur within the same site. For the researcher, knowledge of the staff responsible for each intervention and their caseloads indicates which intervention the client is receiving and therefore the blind is broken once the intervention starts.

The conditions under which the blind can be broken are limited to exceptional circumstances where the practitioner working with the client identifies the need to reveal the intervention. Such cases include situations where the allocated intervention is deemed harmful to the individual, particularly with regard to ancillary services, such as medical care, mental health care or social care. Practitioners will be required to discuss such cases in the first instance with the lead investigator (who is also an employment practitioner).

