### Methods: data collection, management and analysis

#### Data collection methods

Participants are invited, as part of the trial, to complete a range of assessments at several time points (i.e. at baseline, at post intervention / ‘service as usual’ and six-month post-intervention follow-up) in order to measure the impact of the intervention or ‘service as usual’ on key dimensions including self-esteem, hopefulness, resilience and career self-efficacy (Fig. 1).

Each questionnaire (see Additional file 2) is coded with client ID, date of completion, researcher’s name, and questionnaire version (i.e. baseline, T1, T2). Client IDs are generated by the NGO and link to the client’s personal information contained on the NGO’s client database. This will be beneficial to the researcher at the six-month post-intervention phase in order to update data on the intervention or ‘service as usual’ and outcomes.

At baseline (T0), the study is explained to the potential participant and consent is sought (see Additional file 3). The baseline questionnaire is administered, coded and signed by the researcher. At post intervention (T1), the researcher meets with each participant, administers the questionnaire along with a participant update questionnaire which aims to capture information on re-employment, quality of employment, training progression and overall progress (see Additional file 4). This process is repeated at the six-month follow-up (T2).

A tracking file containing participant details—including client ID, completion of questionnaires, appointment dates, guidance practitioner name and outcome updates—will be maintained by the researcher for the duration of the study. Due to the nature of this client group, non-attendance is common and so a tracking system enables the researcher to identify ‘no-shows’, ‘drop outs’ and patterns of attendance. Outcome data for participants who do not continue or who deviate from the intervention or ‘service as usual’ will be documented in this file to study completion.

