MMRM was chosen as the main statistical method for analysis as it can reduce several analytic problems that may arise from the EEPIC study design. First, it has the advantage of modelling change within individuals as well as across groups, thus enabling the isolation of factors contributing to the outcome, such as, age, gender, duration of unemployment or highest educational level (common to both intervention and control condition). Second, it allows for different numbers of measurements per participant, thereby tolerating a level of missing data, which are a particular problem with RCTs as follow-up data are often collected many months after treatment has ended and participants may be difficult to contact [75]. This enables us to use all of the data collected as opposed to deleting cases or imputing missing values. Third, it has the advantage of allowing for different time points for each individual, so data collected for one participant at month 4 can be tested alongside data collected for the next participant at month 6 [76]. Singer and Willet [77] identify this as the best approach for longitudinal data which has three or more time points.

The analysis will follow an intention-to-treat (ITT) principle where all randomised participants, including those who stop receiving the intervention, will be analysed ‘as randomised’. MMRM analysis is a maximum likelihood statistical modelling technique whereby mean estimates and the repeated measures covariance structure for the observed data are based on a statistical model and possible values are generated for the missing data [78]. Attrition will also be analysed to assess the differences between those who ‘dropped out’ and those who stayed, and indeed if there are predictors at baseline to indicate same. MMRM will be used in the main, although t-tests will be employed to detail any significant differences found from the MMRM.

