The trial design has a number of strengths. First, the location of the trial enables access to an existent group of long-term unemployed job-seekers who are in receipt of a Job Seekers payment and who are obligated, therefore, to participate in the Pathways to Work programme/service as usual. This ensures that all potential participants are eligible, meet the inclusion criteria and expect to receive, at a minimum, the service as usual. Second, the data manager performs the randomisation, thereby reducing potential selection bias and participants are assigned thereafter to the intervention or ‘service as usual’ after baseline assessments have been completed. Participants are analysed ‘as randomised’, thereby maintaining participants in their allocated groups and further reducing any selection bias. Delivery of the intervention and ‘service as usual’ with fidelity also aims to limit participants’ likelihood to avoid some aspects of the interventions. Third, all randomised participants will be included in the analysis as per the ITT principle. As detailed earlier, an advantage of the MMRM analysis is that it allows for different numbers of measurements for each participant, and uses all available data, thus minimising attrition bias. Lastly, the researcher (initially) and the participants are blinded thereby reducing potential bias in implementation of the services and in the performance of the participants.

There are, however, also limitations to this study. First and foremost, the duration of intervention and control conditions will vary as individual needs differ. To allow for this, the extent of the intervention or control conditions will be documented in terms of the number of contact hours provided across the number of weeks of engagement with the service. These types of data could benefit the design of a model which promotes individualised approaches. Second, the NGO participating in the trial is implementing government policy, which could change at any time. The study is being conducted in a rapidly changing environment, where neither the NGO nor the researcher has the authority to reverse policy decisions. This leaves the trial vulnerable to external influences beyond our control.

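### The rule that makes participants ineligible if the DSP refers them elsewhere during the trial reaches people already randomised and must be reconciled with the intention-to-treat analysis

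*Protocol article*

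**What the plan says.** Four places in the protocol article bear on this.

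- **Adherence to intervention protocol.** Participants may use other support services, but not other employment services. Those whom the DSP refers to an alternative employment service before entry are ineligible. The same sentence adds those "who are referred during the trial will be ineligible for participation".
- **Statistical methods/analysis.** The analysis is intention-to-treat: "all randomised participants, including those who stop receiving the intervention, will be analysed" in the arm to which they were assigned. The Discussion lists this as a strength: "all randomised participants will be included in the analysis as per the ITT principle".
- **Data collection methods.** On the researcher's tracking file: "Outcome data for participants who do not continue or who deviate from the intervention or ‘service as usual’ will be documented in this file", up to study completion.
- **Discussion, on timing.** "participants are assigned thereafter to the intervention or ‘service as usual’ after baseline assessments have been completed". Sequence generation and implementation gives the same order: consent and questionnaire first, then allocation by the data manager.

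**The concern.** An eligibility criterion decides who may be randomised. Here it is also triggered by an event that can happen afterwards. A person who has been randomised and is then declared ineligible is, on the plain meaning of the word, no longer a trial participant. That does not fit an analysis of all randomised participants.

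What is at stake is who enters the primary comparison. Removing people because of something that happens after allocation loses the protection of randomisation if the event is related to arm or to outcome. The event is a realistic one: the Discussion says that government policy could change at any time and that the trial is exposed to this. The people handling such cases would know the arm. On practitioners, the Blinding section says that "the staff delivering the interventions cannot be blinded", and it says that the researcher, who keeps the tracking file, is unblinded once the intervention starts.

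Trial status reports 140 randomised, which equals the target of 70 per group. Unless recruitment goes beyond target, every further use of the rule falls on someone already randomised.

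**Working it through.** **1. Does the rule reach randomised people?** The sentence itself separates referral before entry from referral during the trial. Allocation comes straight after consent and baseline. The second limb therefore covers the period after randomisation.

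**2. Do the other sections settle what happens to these people?**

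| Section | What it covers | Does it name people made ineligible by referral? |
|---|---|---|
| Adherence to intervention protocol | They are ineligible for participation | Yes, but silent on follow-up and analysis |
| Statistical methods/analysis; Discussion | All randomised, including those who stop the intervention, analysed as randomised | No |
| Data collection methods | Outcomes of those who stop or deviate documented to completion | No |

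Two readings remain open: the trial service ends but follow-up and analysis continue, or the person leaves the trial. Only the first is compatible with intention-to-treat.

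**3. The plan's own figure.** Sample size inputs: d = 0.50, two-sided alpha 0.05, 80% power. The noncentral-t calculation gives 63.77, so 64 per group with power 0.801, as stated. The target of 70 per group allows for a loss of 1 - 64/70 = 8.6%, in line with an allowance of about 10%. With all 70 per group observed, power is 0.836. The point does not depend on these figures.

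**4. Illustrative bias if people are removed.** Assumptions, none of them from the documents: true effect zero, 70 per arm, SD 1, a share f of an arm excluded, and excluded people differing from retained people in the same arm by D SD.

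- With the full-arm mean set to 0, the retained mean is -f x D. The bias in the arm difference therefore has size |f1 - f2| x D.
- SE = sqrt(1/n1 + 1/n2), with n = 70 x (1 - f).
- Two-sided rejection rate (normal approximation) = 1 - Phi(1.96 - bias/SE) + Phi(-1.96 - bias/SE).

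| Excluded, arm 1 vs arm 2 | D | Bias (SD) | False-positive rate |
|---|---|---|---|
| 10% vs 10% | 0.5 or 1.0 | 0 | 5.0% |
| 5% vs 15% | 0.5 | 0.10 x 0.5 = 0.05 | 5.9% |
| 5% vs 15% | 1.0 | 0.10 x 1.0 = 0.10 | 8.7% |
| 5% vs 20% | 0.5 | 0.15 x 0.5 = 0.075 | 7.0% |
| 5% vs 20% | 1.0 | 0.15 x 1.0 = 0.15 | 13.1% |

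Example, second row: n = 66.5 and 59.5, SE = 0.178, bias/SE = 0.28, rejection rate 5.9%. The direction depends on which arm loses more people and on whether those referred are better or worse off. Equal rates remove the bias only if the same kind of person is lost in both arms.

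**5. Illustrative power.** Excluding 10% of 70 leaves 63 per arm and power 0.795. If that 10% comes on top of a 10% attrition loss, 70 x 0.9 x 0.9 = 56.7 per arm and power is 0.752.

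**The case against.** The strongest reply is that the rule speaks of participation, not analysis. It closes a paragraph about which other services participants may attend, so it can be read as ending the trial service only. Someone who stops the service can still be analysed as randomised, the protocol says so twice, and the tracking file is meant to hold outcomes for those who stop or deviate. This reading is reasonable and may well be the intended one. It does not dispose of the point, because the text never states it and the plain meaning of ineligible points the other way. A full SAP is promised before the database is opened, but the trouble is a rule already written, not a detail left for later.

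Several stronger inferences are tempting and not supported:

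- **That participants have been or will be dropped from the analysis.** No section reports or plans such removal.
- **That referral differs by arm.** Service-as-usual contact follows the DSP's PEX timetable and intervention contact follows need, so a difference is plausible. But the timetable governs meetings, not onward referral, and both services run in the same NGO.
- **That the bias could reach 0.20 SD.** This needs 20% removed from one arm, none from the other, and D = 1.0. The rule applies to both arms.
- **That the mixed model cannot help.** If people are kept but miss later visits, it uses their available data and is valid under missing at random. It fails if their data are deleted or the missingness is informative.
- **That power falls to 75%.** The arithmetic is right, but it stacks an assumed further 10% loss on the planned allowance, and the Sample size section does not say that the allowance leaves such losses out.

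**Conclusion.** The point holds as a badly fixed rule. As worded, the referral criterion applies after randomisation and conflicts with the stated as-randomised analysis, and no section says that those affected stay in T1 and T2 follow-up and in the analysis. This conclusion rests on the text alone.

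The consequence is conditional. Bias arises only if people are actually removed and if referral rates, or the kind of person referred, differ by arm. Under the assumptions shown (5% against 15-20% excluded, D of 0.5-1.0 SD) it is about 0.05-0.15 SD, or 10-30% of the 0.50 SD target effect. With equal removal of similar people it is zero. The documents give neither a referral rate nor a difference between referred and retained participants, so these figures show scale and are not estimates.

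**What to change.** Reconcile the sections before the SAP is issued and the database opened:

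1. Limit the referral criterion to referrals made before randomisation.
2. State that participants referred elsewhere after randomisation are still invited to T1 and T2 and are analysed in their allocated arm with all available data. Whether they go on receiving the trial service is a separate matter that the analysis rule need not decide.
3. Record each such referral and its date in the existing tracking file, and report the numbers by arm. Any analysis without these people should be a sensitivity analysis only.
4. Check whether anyone among the 140 has been removed under this rule and, if so, restore them to the analysis set with the data they have.

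The cost is a sentence or two in the protocol or SAP and follow-up of a few more people with existing staff and records. Sample size and model are unchanged.

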### Control group: ‘service as usual’

Control group participants receive the ‘service as usual’ as provided nationally by the DSP’s Intreo service, the Irish state public employment service. This service is also delivered within the NGO and consists of a number of steps:*Step 1:* Once the individual has attended a GIS, a first appointment is made, the timing of which is determined by the individual’s score on a statistical profiling model, ‘PEX’, which can be classified as ‘low’, ‘medium’ or ‘high’. The ‘Probability of Exit’ or ‘PEX’ profile, introduced in October 2012, is based on a number of factors including: history of long-term unemployment; age; number of children; level of education; literacy/numeracy issues; urban living; transport availability; levels of labour market engagement; spousal earnings; and geographic location. All of these can affect a person’s probability of remaining unemployed for 12 months or more and therefore becoming classified as ‘long-term unemployed’ [59]. Clients who have a low probability of exiting the live register within the coming 12 months receive more frequent interaction with the employment services than those classified as having a high probability of leaving the live register and accessing the labour market.‘High PEX’ clients are invited to attend a meeting with a case officer six months after attendance at the GIS.‘Medium PEX’ clients attend within two weeks.‘Low PEX’ clients attend immediately.

At this first appointment, the client and case officer agree a number of steps or goals which the client commits to undertake as part of a Personal Progression Plan (PPP). This plan is signed and becomes the client’s responsibility to fulfil. Within the current study, case officers are also required to use the *Cantril’s Ladder* scale at the first appointment to assess the client’s perceived progress towards the labour market.*Step 2:* Case officers decide on and conduct systematic follow-ups (e.g. phone call, email, text) after the first meeting in order to ‘check in’ with the client and to see how they are progressing. The level of contact is normally agreed in the PPP and a follow-up category is set in the Client Services System (i.e. the DSP’s IT database) which calculates when the client is due for systematic follow-up.*Step 3:* The case officers are required to conduct Activation Review Meetings (ARM) by the DSP which can include a phone call or a face-to-face meeting to review progress of the tasks identified and agreed in the PPP. This is essentially a monitoring meeting and the timing of these meetings is dependent on the client’s initial PEX score:‘High PEX’ clients receive an ARM meeting at six months and every three months thereafter;‘Medium PEX’ clients receive an ARM meeting every three months;‘Low PEX’ clients receive an ARM meeting every two months;Under 25 s (High, Medium and Low PEX) receive monthly ARM meetings.

Within the current study, case officers will also be required to use Cantril’s Ladder at the ARM meeting to assess perceived progress towards the labour market.

